**Methods:**

To investigate the efficacy of CFT compared with a sham intervention for pain intensity and disability post-intervention (immediately after the last session) in patients with non-specific chronic low back pain (CLBP). This study is a randomized controlled trial in which 152 (18–60 years old) patients with CLBP will be enrolled. The patients will be randomly allocated to receive (1) CFT intervention or (2) sham intervention. The experimental group will receive individualized CFT in a pragmatic manner (5 to 7 sessions) based on the clinical progression of the participants. The sham group will attend six sessions: consisting of 30 min of photobiomodulation using a detuned device and more than 15 min of talking about neutral topics. Patients from both groups also will receive an educational booklet (for ethical reasons). Participants will be assessed pre and post-intervention, 3 months, and 6 months after randomization. The primary outcomes will be pain intensity and disability post-intervention. The secondary outcomes will be: pain intensity and disability at 3- and 6-month follow-up, as well as self-efficacy, global perceived effect of improvement, and functioning post-intervention, 3-, and 6-month follow-up. The patients and the assessor will be blinded to the treatment administered (active vs. sham).

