### Outcome measures

The primary outcomes in the current study will be pain intensity [32] and low back pain-related disability [27] collected post-intervention. The secondary outcomes will be pain intensity and low back pain-related disability at 3 and 6 months after randomization, as well as self-efficacy [33], global perceived effect of improvement [32], and functioning [32] post-intervention, 3, and 6 months after randomization. In the baseline, we will administer scales to assess moderating effect: expectation [34], depression [35], anxiety [36], kinesiofobia [37], and pain catastrophizing [38]. Mini-Mental State Examination (MMSE) [39] will be administered to assess the cognitive function of the volunteers. Patients with a score lower than 24 will be excluded [40]. The questionnaires will be administered in an assisted interview mode.

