### Statistical analysis

All randomized patients will be analyzed on an intention-to-treat basis. Baseline characteristics will be presented by the treatment group. Binary and categorical variables will be summarized by frequencies and percentages. The between-group differences (effects of treatment) and their respective 95% CIs will be calculated by constructing linear mixed models. Treatment effect for the primary and continuous secondary outcomes will be estimated using mixed linear models, considering the correlation within the individual. The mixed linear model will include random intercept adjusted with the baseline score, time as categorical, and the interaction between treatment and time. We will use strategies to reduce the attrition rate during follow-ups as telephone calls and an active search of information.

Two primary outcome variables were considered for the calculation of sample size. For pain intensity, an improvement of at least 1-point on the NPRS (SD=1) and a mean difference of at least 5 points for the ODI score (SD=10). The following specifications were considered: α=5%, 80% statistical power, effect size of 0.27 for *F*-test, and a follow-up attrition rate of 15%. The final sample size will be comprised of 152 patients (76 per group) (G*Power©, University of Dusseldorf, Germany). A moderator effect of baseline variables including the expectation to treatment will be calculated using regression analysis and structural equation modeling (*path analysis*) (AMOS (SPSS, v.22). Data will be coded and entered into the Statistical Package for the Social Sciences (SPSS), version 22 (Chicago, IL, IBM corp., USA) program for analysis and the significance level will be established at 0.05. The Bonferroni correction will be used to adjust the *p*-values for multiple primary outcomes [47]. The data collected will be stored and coded to protect patient confidentiality. In order to handle missing data, we will replace the value with the last observation carried forward. The researchers involved in the study will have access to the final trial dataset and, upon request, it can be shared for the purposes of results conference and publication. The results of the study will be disseminated to interested parties through publications in an appropriate journal.

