## Discussion

The pain and disability related to CLBP may compromise many aspects of individual daily life. Non-specific CLBP is best seen as neurobiological and behavioral responses to individuals’ actual and/or perceived threat to their body, lifestyle, or social circumstances and/ or disruption to their homeostasis. In such a scenario, CFT was developed to consider these interacting processes involved in CLBP which demands a flexible multidimensional clinical reasoning framework [9].

Despite its promising approach centered on the biopsychosocial model, there are few RCTs available in the literature [10–12], and the majority are conducted always by the same researcher group, noteworthy are the limitations of the first trials [48, 49]. The RCTs previously published [10–12] showed high attrition rates during follow-up (greater than 24%), failed to follow the intention-to-treat principles, and to blind assessors involved in the follow-up assessments.

To the best of our knowledge, the current study will be the first to compare CFT vs. sham intervention. Sham-controlled RCTs may help to understand the influence of non-specific factors on treatment outcomes. Considering complex interventions as CFT, it is imperative to understand the impact of contextual factors on outcomes.

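### Last observation carried forward turns a missing primary outcome into the baseline score and pre-empts the planned mixed model

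*Protocol article*

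**What the plan says.** All references are to the protocol article.

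- **Missing data** (Statistical analysis): "In order to handle missing data, we will replace the value with the last observation carried forward". The rule has no exception by visit or outcome, is not labelled as a sensitivity analysis, and no alternative is named.
- **Model** (same section): "Treatment effect for the primary and continuous secondary outcomes will be estimated using mixed linear models, considering the correlation within the individual". Its terms are then given: "The mixed linear model will include random intercept adjusted with the baseline score, time as categorical, and the interaction between treatment and time".
- **Population** (same section): "All randomized patients will be analyzed on an intention-to-treat basis".
- **Expected loss** (same section): "a follow-up attrition rate of 15" per cent. The visit to which it applies is not stated.
- **Visits** (Abstract, Methods): "Participants will be assessed pre and post-intervention, 3 months, and 6 months after randomization".
- **Primary time point** (Outcome measures): "The primary outcomes in the current study will be pain intensity [32] and low back pain-related disability [27] collected post-intervention".
- **Earlier CFT trials** (Discussion): they are criticised because they "showed high attrition rates during follow-up (greater than 24%), failed to follow the intention-to-treat principles".

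**The concern.** The only assessment before the primary visit is baseline. For a patient lost before that visit, LOCF therefore records a change of exactly zero on both pain and disability. The Background section says the control arm is there to capture regression to the mean, natural course and placebo response. LOCF assigns none of these to a patient who drops out, although entry thresholds on pain (NPRS 3 or more) and disability (ODI above 14%) make some regression to the mean likely.

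The rule also undercuts the model it accompanies. A likelihood-based mixed model uses all observed outcomes and is valid when data are missing at random. If the gaps are filled first, the model has nothing left to handle and counts the filled values as real observations. A patient who misses only the post-intervention visit is given the baseline score, although the 3- and 6-month values could inform the missing one. For the global perceived effect, which is collected only after baseline, there is nothing to carry forward to the post-intervention visit.

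At stake are the estimate, confidence interval and error rate for both primary outcomes.

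**Working it through.** **Inputs from the protocol article.** 76 patients per arm; planned ODI effect 5 points with SD 10; planned NPRS effect 1 point; 15% attrition; Bonferroni over two primary outcomes, so 0.05/2 = 0.025 each.

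**Assumptions (not in the document).** Baseline-to-post correlation 0.5; sham-arm ODI improvement of 0, 5 or 10 points; the loss in each arm at the primary visit; missingness at random within arm.

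**Step 1: the plan's own figure.** An ODI effect of 5/10 gives d = 0.5, f = 0.25. At two-sided 5% and 80% power the two-group F-test needs 64 per arm. 64/0.85 = 75.3, rounded up to 76, or 152 in total, which matches the plan. (The stated f = 0.27 would give 55 per arm, then 65, or 130 in total. That is a separate matter.) So 152 already pays for 15% loss, about 0.15 × 152 = 22.8 patients, and no imputation is needed to recover the sample size.

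**Step 2: expected estimate under LOCF at the primary visit.** Let c be the mean improvement in the sham arm, δ the true additional improvement with CFT, and p the proportion missing in each arm. Missing patients contribute zero change, so

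E(estimate) = (1 − p_CFT)(c + δ) − (1 − p_sham)c.

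With equal loss this is (1 − p)δ, whatever c is:

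- 5% loss: ODI 0.95 × 5 = 4.75.
- 15% loss: ODI 0.85 × 5 = 4.25; NPRS 0.85 × 1 = 0.85.
- 24% loss (the lower bound quoted for earlier trials): ODI 0.76 × 5 = 3.80; NPRS 0.76.

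With unequal loss, for ODI:

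- δ = 5, c = 10, CFT 20% / sham 10%: 0.80 × 15 − 0.90 × 10 = 3.0.
- δ = 5, c = 10, CFT 10% / sham 20%: 0.90 × 15 − 0.80 × 10 = 5.5.
- δ = 5, c = 5, CFT 10% / sham 20%: 0.90 × 10 − 0.80 × 5 = 5.0 (the errors cancel).
- δ = 0, c = 10, CFT 10% / sham 20%: 0.90 × 10 − 0.80 × 10 = 1.0 (false benefit).

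**Step 3: simulation.** Baseline-adjusted regression of post-intervention ODI, 76 per arm, with missing values either set to baseline or left out. Left out, the estimate is unbiased in every scenario. Coverage is for nominal 95% intervals.

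| True effect | Loss CFT / sham | Sham improvement | LOCF estimate | LOCF coverage | Rejection rate, LOCF | Reference |
|---|---|---|---|---|---|---|
| 5 | 5% / 5% | 5–10 | 4.7–4.8 | about 95% | 84–87% at 0.025 | about 88% on observed data |
| 5 | 15% / 15% | 0–10 | 4.2–4.3 | 91–93% | 81% down to 70% at 0.025 | about 84% on observed data |
| 5 | 20% / 10% | 5–10 | 3.5 down to 3.0 | 73–83% | 48–70% at 0.05 | about 90% on observed data |
| 0 | 15% / 15% | 10 | 0 | – | 5.1% at 0.05 | nominal 5% |
| 0 | 10% / 20% | 5–10 | 0.5–1.0 | – | about 3–6% at 0.025 | nominal 2.5% |
| 0 | 5% / 25% | 10 | 2.0 | – | about 19% at 0.025 | nominal 2.5% |

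For the 10% / 20% row with sham improvement 10, the type I error at 0.05 is 10–11%.

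**The case against.** The case for leaving the rule alone has five parts.

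1. **Loss at the primary visit may be well below 15%.** The attrition figure is for follow-up, which runs to 6 months, whereas the primary visit comes after about 5 to 7 weekly sessions. The plan also has weekly reminders, telephone calls and active searching. With 5% loss per arm the harm is slight. This stands, and it limits the size.
2. **Unequal dropout is hypothetical.** Nothing in the document predicts a 20/10 split either way. This also stands. Unequal loss is nevertheless plausible, because the arms differ in nature and the Blinding section concedes that patient blinding may fail.
3. **LOCF is conservative.** With equal loss the error is towards no effect, and with equal loss and no true effect there is no bias. But more loss in the sham arm can inflate the effect or create one, so conservatism cannot be relied on.
4. **LOCF keeps every randomized patient.** With baseline as a covariate, the planned model learns nothing from a patient with no post-baseline value, so deleting LOCF alone would leave a gap against the intention-to-treat statement. This is a fair point about the remedy. It is met by moving baseline into the outcome vector or by multiple imputation, neither of which forces zero change.
5. **The simulation favours observed data.** Dropout is random within arm, so the observed-data analysis is unbiased by construction, and one visit is modelled rather than the full repeated-measures model. True, but LOCF is biased even under this mild mechanism. Loss of coverage at 3 and 6 months follows from the same reasoning and was not simulated.

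The rule is stated outright, so it cannot be treated as detail left to an analysis plan that is not shown.

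**Conclusion.** The concern holds. LOCF is the only stated rule for missing outcomes. At the primary visit it is baseline carried forward, and it displaces a model that would use the observed data better. The proportional shrinkage under equal random loss is exact arithmetic: 15% loss at the primary visit removes 15% of the effect. The direction and size in practice depend on dropout by arm and on the sham-arm improvement, neither of which is known in advance. The range runs from little harm (5% equal loss) to a type I error more than double the nominal level (20% sham / 10% CFT, sham improvement 10). Confidence in the defect is high; confidence in any one size is limited by the assumed correlation, sham response and loss at the primary visit. It should be corrected before analysis because it governs both primary outcomes.

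**What to change.** Remove the LOCF sentence and state instead:

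- The primary analysis is the likelihood-based mixed model on all observed outcomes, under missing-at-random, with no prior single imputation.
- To keep patients with no post-baseline value in the intention-to-treat set, baseline enters as part of the outcome vector, with arm means constrained equal at baseline. Multiple imputation by arm is an acceptable alternative.
- A delta-adjusted sensitivity analysis examines departures from missing-at-random, with the shift allowed to differ by arm.
- LOCF, if kept at all, is a labelled sensitivity analysis, and is not applied to the global perceived effect at post-intervention.

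The cost is a few lines of wording and a little analysis time. Visits, patients and sample size are unchanged, since 152 already allows for 15% loss.

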## Discussion

The pain and disability related to CLBP may compromise many aspects of individual daily life. Non-specific CLBP is best seen as neurobiological and behavioral responses to individuals’ actual and/or perceived threat to their body, lifestyle, or social circumstances and/ or disruption to their homeostasis. In such a scenario, CFT was developed to consider these interacting processes involved in CLBP which demands a flexible multidimensional clinical reasoning framework [9].

Despite its promising approach centered on the biopsychosocial model, there are few RCTs available in the literature [10–12], and the majority are conducted always by the same researcher group, noteworthy are the limitations of the first trials [48, 49]. The RCTs previously published [10–12] showed high attrition rates during follow-up (greater than 24%), failed to follow the intention-to-treat principles, and to blind assessors involved in the follow-up assessments.

To the best of our knowledge, the current study will be the first to compare CFT vs. sham intervention. Sham-controlled RCTs may help to understand the influence of non-specific factors on treatment outcomes. Considering complex interventions as CFT, it is imperative to understand the impact of contextual factors on outcomes.

## Trial status

Protocol: The study was registered prospectively on ClinicalTrials.gov (Protocol Number: NCT04518891). Last Update Posted: June 18, 2021.

Date recruitment began: May 17, 2021

Approximate date when recruitment will be completed: July 17, 2023

## Data Availability

The datasets used and/or analyzed during the current study will be available from the corresponding author on reasonable request.

## Abbreviations

CFT: Cognitive functional therapy
CLBP: Chronic low back pain
RCTs: Randomized clinical trials
NPRS: Numerical pain rating scale
CONSORT: Consolidated Standards of Reporting Trials
SPIRIT: Standard Protocol Items: Recommendations for Interventional Trials
TIDieR: Template for Intervention Description and Replication
MCDID: Minimum clinically important difference
ODI: Oswestry Disability Index
PSEQ: Pain Self-Efficacy Questionnaire
GPE: Global Perceived Effect of improvement with treatment
STES: Standford ExpectationTreatment Scale
PHQ-9: Patient Health Questionnaire 9-item
TKS: The Tampa Scale for Kinesiophobia
PCS: Pain catastrophizing scale
SPSS: Statistical Package for the Social Sciences
SD: Standard deviation
